### Ethical Considerations

The Sentinel project will be conducted in full accordance with the Declaration of Helsinki, relevant national regulations, institutional policies, and the European General Data Protection Regulation (Regulation [EU] 2016/679).

All participating health care professionals will receive detailed written information describing the study aims and procedures, voluntary nature of participation, data collected, confidentiality safeguards, and right to withdraw without consequences. Written informed consent will be obtained before participation in training evaluations, usability assessments, and research data analysis.

The registry will not collect direct identifiers of children, families, or caregivers. Only anonymized or non–directly identifiable variables necessary for research and service evaluation will be entered. The registry will be separated from clinical records and will not replace institutional case files or mandatory legal reporting. Information collected for the study will be used exclusively for research, audit, and service improvement purposes approved by the ethics committee without any adverse clinical or administrative consequences for children or families.

The project protocol will be submitted for review and approval by the ethics committee of the coordinating hospital (Comitato Etico Territoriale [CET] Lombardia Area 1_2025). Participation in the study does not entail direct clinical risk for professionals and does not add costs for the health care system beyond planned project activities. Because the topic involves highly sensitive child protection information, access privileges, audit trails, password protection, secure storage, and anonymized exports will be used to minimize privacy and confidentiality risks.

All training and data collection activities will be conducted in a manner that protects dignity, safety, privacy, and confidentiality. Mandatory reporting obligations and urgent child protection actions will remain governed by existing laws and institutional procedures; participation in the Sentinel project will not delay or modify any duty to report suspected maltreatment.

The study protocol was registered in ClinicalTrials.gov (ID NCT07250074). If modifications to the original protocol are required, amendments will be submitted to the ethics committee for approval before implementation, and the approved information will be updated on ClinicalTrials.gov.

To ensure greater scientific rigor, the manuscript was prepared in accordance with the SPIRIT (Standard Protocol Items: Recommendations for Interventional Trials) guidelines for reporting study protocols.

## Results

The study was funded in September 2025, and ethical approval was obtained in January 2026. Participant recruitment and data collection began in April 2026 and are currently ongoing. Data analysis has not yet started. Completion of data collection and publication of the results are expected between December 2027 and January 2028.

### Registry Phase Results

The registry component will generate implementation results on the use of the REDCap platform for systematic, secure, and standardized recording of suspected child maltreatment reports [45]. Reported results will include the number of trained users, number of active registry users, number of records created, completion of mandatory fields, time required for report completion, and number of technical or workflow issues identified during implementation.

The analysis will describe whether the registry provides a more unified view of suspected cases and care pathways than the preimplementation documentation process. Completeness, traceability, documented actions, follow-up fields, and pathway activation will be used as operational indicators of report quality.

Registry usability will be described using SUS scores, reported as means, SDs, medians, IQRs, 95% CIs, and the proportion of scores below 70 and above 80 [44]. To evaluate implementation, reporting rates will be compared before and after registry introduction and expressed as reports per professional month and, where denominators are available, per 1000 pediatric contacts.

The registry will describe suspected cases by maltreatment type, child characteristics, family and social context, access route, setting, referral pathway, follow-up, and outcome. These data will help assess whether the model can generate useful local information to support prevention strategies, service indicators, and health care planning.

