### Aim of the Study

The aim of this study is to evaluate the usability, feasibility, and preliminary implementation impact of the Sentinel digital registry and training network in improving standardized case identification, documentation quality, reporting timeliness, and case management among hospital and community pediatric health care professionals.

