## Methods

### Study Design

The Sentinel study is an observational, exploratory, monocentric pilot implementation study with a pretest-posttest evaluation design and an overall duration of 24 months. The project does not introduce an experimental clinical treatment and does not modify the legal or clinical duties of professionals involved in suspected child maltreatment. Rather, it evaluates the implementation of 2 organizational tools: a secure digital registry for standardized documentation and a structured training program for pediatric health care professionals. The primary objective is to assess registry usability and feasibility. Secondary objectives are to evaluate training effectiveness, reporting completeness, reporting timeliness, and preliminary changes in suspected maltreatment reporting rates before and after implementation.

The project is organized into 2 interconnected components: the registry component and the training component. These components will be implemented sequentially and then evaluated jointly because the registry is intended to standardize documentation, whereas training is intended to improve recognition, case management confidence, and appropriate use of the registry.

The operational sequence will include development and internal testing of the REDCap registry; definition of the minimum dataset and reporting workflow; recruitment of hospital and community pediatric professionals; baseline assessment of knowledge, competencies, and reporting activity; delivery of the training program; activation of registry data entry; continuous monitoring of registry completeness and technical issues; follow-up assessment of outcomes; statistical analysis; and dissemination of results. All activities will be coordinated by an internal scientific committee responsible for methodological quality, ethical compliance, data protection procedures, and adherence to project timelines.

Because of its observational and pilot implementation nature, the study will not interfere with clinical decision-making, child protection duties, or mandatory reporting obligations. Professionals will continue to follow existing institutional and legal procedures for suspected maltreatment. Study data will be used only to evaluate registry use, reporting activity, and educational outcomes and identify preliminary indicators of feasibility, usability, acceptability, and implementation impact that can inform future multicenter or regional surveillance models.

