### Implementation Components and Procedures

#### Registry Component

The digital registry will be developed using the REDCap platform, a system widely used in clinical research for secure data collection, management, and analysis. The registry will be configured with role-based access, audit trails, structured data entry fields, mandatory and optional variables, and data quality checks. Access will be restricted to authorized project personnel, and all data management procedures will comply with applicable institutional policies and data protection regulations.

The registry will collect only anonymized or non–directly identifiable information required for research and service evaluation. Data fields will include child age group and sex, date and setting of contact, type of suspected maltreatment (physical, psychological, or sexual maltreatment; neglect; or exposure to domestic violence), warning signs, risk and protective factors, reporting source, referral or follow-up arrangements, and case management outcome. Each record will be assigned a unique alphanumeric study code. Direct identifiers, such as name, fiscal code, address, telephone number, or full date of birth, will not be entered into the research registry. Potential duplicate reports will be managed through predefined nonidentifying linkage variables, including time window, age group, sex, setting, and event characteristics, without attempting to reidentify the child.

Registry usability will be evaluated using the System Usability Scale (SUS), a validated 10-item questionnaire yielding scores from 0 to 100 [44]. SUS completion will be restricted to trained and authorized professionals with documented exposure to the registry, as detailed in the Outcomes and Measurement Time Points section. Feasibility indicators will include number of active users, number of records created, proportion of completed mandatory fields, average time required to complete a report, number of technical support requests, proportion of records with documented pathway activation, and completeness of follow-up fields. These indicators will allow for evaluation of whether the registry reduces data fragmentation and supports standardized clinical and operational terminology.

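### The registry's documentation-quality indicators are measured only after activation, yet the article uses them for a before-after claim and states no preimplementation measure of documentation quality

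*Protocol article*

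**What the plan says.** Two places in the Protocol article promise a comparison on documentation. Registry Component lists feasibility indicators, among them "proportion of completed mandatory fields", "proportion of records with documented pathway activation, and completeness of follow-up fields", and then states: "These indicators will allow for evaluation of whether the registry reduces data fragmentation and supports standardized clinical and operational terminology". Registry Phase Results says the analysis will describe "whether the registry provides a more unified view of suspected cases and care pathways than the preimplementation documentation process". The next sentence there reads: "Completeness, traceability, documented actions, follow-up fields, and pathway activation will be used as operational indicators of report quality".

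The Aim of the Study speaks of "improving standardized case identification, documentation quality, reporting timeliness, and case management", under the broader purpose of evaluating usability, feasibility and preliminary implementation impact.

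On the baseline side, Study Design lists "baseline assessment of knowledge, competencies, and reporting activity". Outcomes and Measurement Time Points adds a general sentence that baseline data are collected before training and before the registry is activated. It does not say which documentation variables are meant or where they would come from.

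**The concern.** To say that fragmentation has been reduced, or that the view of cases is more unified than before, one must know how things stood before. The indicators offered for this belong to a tool that does not exist in the preimplementation period. If the plan is followed as written, the report can give a level of completeness after activation but has nothing to set it against.

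At stake is the conclusion on documentation quality, which is part of the stated aim. It also matters downstream, because Overall Evaluation Outcomes intends the performance indicators to support regional quality benchmarks. The Limitations section discusses the quality and completeness of registry data but does not mention that a preimplementation value is lacking.

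**Working it through.** The article gives no figure to reproduce. The check is to trace each named quality indicator to its definition and then look for a preimplementation measurement of it.

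| Indicator (Registry Phase Results) | Definition given elsewhere | Stated preimplementation measurement |
|---|---|---|
| Completeness | Mandatory fields completed (Registry Component); fully completed registry forms (Overall Evaluation Outcomes) | None; cannot exist before activation |
| Follow-up fields | Completeness of the registry's follow-up fields (Registry Component) | None; the fields cannot exist earlier, but whether follow-up was documented could be observed |
| Pathway activation | Share of registry records documenting it (Registry Component) | None stated; the event itself could be observed earlier |
| Traceability | No further definition or source | None |
| Documented actions | No further definition or source | None |

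Result: 0 of 5 indicators have a stated preimplementation measurement.

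Next, the before-after analyses that the article does specify:

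- Knowledge and competency scores: paired tests (Statistical Analysis, Overview). These concern the professionals, not the documentation.
- Reporting rates: Poisson regression, with reports per professional month as the main denominator (Statistical Analysis, Overview; also Registry Component and Registry Phase Results). This counts reports and says nothing about what each one contains.

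No section describes abstraction of earlier case documentation. Ethical Considerations keeps the registry apart from clinical records.

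The consequence can be written simply. The change in a documentation indicator is

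change = P_post − P_pre.

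Take P_post = 85%, an assumed value for illustration that is not in the documents. With P_pre unobserved it may lie anywhere from 0% to 100%, so the change lies between 85 − 100 = −15 and 85 − 0 = +85 percentage points. Even its sign is not determined. A confidence interval around P_post does not help, because it describes sampling error in the level and not the change. For mandatory-field completion the position is weaker still, since P_pre is not defined at all.

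Finally, high completeness is partly produced by the tool. Registry Component provides for mandatory variables and data quality checks, and Data Management, Confidentiality, and Registry Workflow has the research team review mandatory fields and resolve missing mandatory information. A high post-activation value is therefore to be expected whatever the earlier documentation was like.

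**The case against.** The case on the other side has several parts.

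- **Some of these items are not confined to the registry.** Outcomes and Measurement Time Points lists follow-up documentation and pathway activation as reporting outcomes, apart from the feasibility indicators, and the general baseline sentence follows. Overall Evaluation Outcomes uses reports and cases as denominators. Mandatory reporting runs through existing institutional channels. This stands. A reader might infer that every quality indicator exists only in the registry, so that no comparator is possible; the documents do not support that. What they support is that no baseline measurement of these items is specified.
- **The text says only that it will describe.** This also stands: no test of documentation quality is planned, and Registry Phase Results does not expressly tie the five indicators to the comparison with the earlier process. But a descriptive comparison still has two sides, and Registry Component does tie its own indicators to reduced fragmentation.
- **Open-text answers could inform the comparison.** They are to be grouped under themes that include workflow integration. They could support a statement about what users perceive, but the article does not assign them this role.
- **Detail may sit in a fuller protocol.** That would answer a complaint about omitted detail. Here, however, the article itself lists its baseline content and its before-after analyses, and these do not match the comparison it promises.
- **It is a pilot.** Sample Size Calculation says that results are estimates for future studies, not definitive evidence. That moderates the claims, but a change without a before value cannot be estimated even provisionally.
- **The aim concerns preliminary impact.** This is fair, and the aim need not be rewritten as if it were a planned conclusion.

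**Conclusion.** The point holds in a limited form. The article draws, or promises, a before-after reading of documentation from indicators that are measured only after activation, and it states no preimplementation measure or source for documentation quality. Completeness of registry fields cannot have a before value. Follow-up documentation and pathway activation could have one, but none is specified.

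A reader might go further and infer that registry completeness will be reported as an improvement. The documents do not say so; they list it as a feasibility and performance indicator. The risk arises from the sentence in Registry Component that lets those indicators speak to reduced fragmentation.

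The reach is confined to the conclusion on documentation. The System Usability Scale outcome, the sample size, the knowledge comparison and the reporting-rate model are untouched. The conclusion assumes that the baseline content listed in Study Design is what will be collected, with reporting activity meaning the report counts needed for the rate. If it is meant to include follow-up and pathway status, the article should say so.

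**What to change.** 1. In Registry Component and Registry Phase Results, present completeness, traceability and follow-up-field indicators as post-activation descriptives with 95% CIs. Remove reduced fragmentation, and a more unified view than the earlier process, as conclusions drawn from them.
2. Keep a before-after statement only for items such as follow-up documented (yes/no) and pathway activated (yes/no), and only if they are scored in the same way on the baseline reports already counted for the reporting rate. Name the source of those baseline reports.
3. The Aim of the Study may stand if documentation quality is marked there as described and not compared.

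The wording change needs no new data and can still be made, since the Results section says that data analysis has not started. Its price is a less favourable claim. The option in item 2 adds a short check of a small number of baseline reports. It assumes that those reports can be consulted for this purpose, and as a protocol change it would go through the amendment route described under Ethical Considerations.

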### Training Phase Results

The analysis will examine whether theoretical and practical training improves participants’ ability to recognize early warning signs of abuse or neglect, communicate with children and families using trauma-informed principles, select appropriate reporting procedures, and complete the registry accurately.

The training evaluation will report Likert-scale satisfaction scores, perceived usefulness, perceived transferability to clinical practice, and confidence in using the registry [46]. Open-ended responses will be analyzed thematically to identify perceived strengths; barriers; suggestions for improvement; and key issues related to clinical relevance, content clarity, registry usability, reporting procedures, and coordination with social and child protection services. These qualitative data will complement quantitative outcomes and support refinement of the training model.

Overall, the training results will indicate whether the project can consolidate a network of informed and coordinated professionals, so-called Sentinel pediatricians, capable of supporting surveillance activities and sustaining standardized procedures beyond the initial pilot phase.

### Overall Evaluation Outcomes

Integrated statistical analysis of registry and training data will describe the feasibility, usability, acceptability, and preliminary implementation impact of the combined registry training system as a prevention and monitoring model.

Performance indicators will include average reporting time, percentage of fully completed registry forms, proportion of reports with documented follow-up, proportion of cases with activation of child protection pathways, number of duplicate or repeat reports, and rate of active participation of professionals in the platform.

The elaboration of these data will provide a solid foundation for defining regional quality benchmarks in the management of suspected child maltreatment cases, identifying replicable best practices and areas for improvement. Quantitative and qualitative results, interpreted in an integrated manner, will also validate the project’s methodological model, confirming its feasibility and transferability to other regional or national contexts.

From a scientific standpoint, Sentinel will produce preliminary evidence on the feasibility of digital registries in pediatrics and on the contribution of multidisciplinary training to early detection and standardized documentation of suspected child maltreatment. The data collected will be disseminated through reports and peer-reviewed publications, contributing to the international literature on child protection and digital health.

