### Hypothesis and Rationale of the Project

In light of these critical issues, the Sentinel project was conceived to create an integrated surveillance and training system for the early recognition of suspected child maltreatment, combining technological innovation, professional education, and hospital-community coordination.

The underlying hypothesis is that the combination of a standardized digital registry and a structured training program for pediatricians and health care professionals can significantly improve the capacity of the health care system to identify, document, and respond to cases of suspected maltreatment. Specifically, the project assumes that this integrated approach will (1) enhance the early detection of suspected child abuse and neglect; (2) improve the quality, completeness, and timeliness of reporting; and (3) strengthen collaboration between hospital and community-based services, thereby increasing the efficiency of multidisciplinary care for vulnerable children.

The registry, developed using the REDCap platform (Vanderbilt University), will enable the anonymous and standardized collection of clinical and social data while ensuring data security, traceability, and compliance with privacy regulations.

In parallel, the training component, structured through theoretical and practical modules, will provide health care professionals with the clinical, communication, legal, and operational skills required to recognize warning signs, activate reporting pathways, document case information, and use the registry appropriately. This dual approach is designed to promote a shared language and a consistent, evidence-based methodology among pediatric and allied health professionals.

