The impact of the integrated registry training system on suspected maltreatment reporting will be assessed by comparing pre- and postimplementation reporting rates. The numerator will be the number of suspected maltreatment reports recorded during each observation period. The denominator will be the number of participating professionals and, when available, the number of pediatric consultations or service contacts during the same period. Reporting rates will therefore be expressed as reports per professional month and, where denominators are available, reports per 1000 pediatric contacts.

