### Outcomes and Measurement Time Points

The primary outcome is registry usability, measured using the mean SUS score collected after participants use the registry. Specifically, the SUS will be administered once at the end of the 12-month registry activation and follow-up period or earlier for participants who discontinue participation after having completed the minimum required registry exposure. Eligible respondents will be trained and authorized hospital or community professionals involved in suspected maltreatment recognition, documentation, or case management. To ensure that SUS responses reflect actual exposure to the tool, participants will be included in the primary SUS analysis only if they have entered at least one registry record or completed at least one supervised registry use session or simulation. Participants without any registry exposure will not contribute to the primary SUS analysis.

Secondary outcomes include feasibility indicators (active users, number of records, completion of mandatory fields, technical support requests, and time to complete a report), training outcomes (pretest-posttest knowledge and competency scores, satisfaction, and qualitative feedback), and reporting outcomes (number and rate of suspected maltreatment reports, reporting timeliness, duplicate reports, follow-up documentation, and activation of child protection pathways). Baseline data will be collected before training and registry activation, posttraining outcomes will be collected immediately after training, and registry usability and implementation outcomes will be collected during registry use and at the end of the observation period.

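### The article promises evidence on training's contribution to early detection, but no stated outcome measures earliness, and the reporting rate cannot separate better recognition from a lower reporting threshold, or training from the registry

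*Protocol article*

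**What the plan says.** The first hypothesis, under Hypothesis and Rationale of the Project, is that the integrated approach will "enhance the early detection of suspected child abuse and neglect". Overall Evaluation Outcomes then says that "Sentinel will produce preliminary evidence on the feasibility of digital registries in pediatrics and on the contribution of multidisciplinary training to early detection", and extends the same claim to standardised documentation of suspected cases.

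The reporting outcomes, under Outcomes and Measurement Time Points, are "number and rate of suspected maltreatment reports, reporting timeliness, duplicate reports, follow-up documentation, and activation of child protection pathways". The Registry Component section says that the system's impact "on suspected maltreatment reporting will be assessed by comparing pre- and postimplementation reporting rates", and defines the count: "The numerator will be the number of suspected maltreatment reports recorded during each observation period". The Statistical Analysis overview models this count by Poisson regression per professional month, adding a model per 1000 contacts where service volumes are available.

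On the two components, Study Design says: "These components will be implemented sequentially and then evaluated jointly". The registry fields include "referral or follow-up arrangements, and case management outcome". The Training Component section adds a knowledge and competency questionnaire with clinical scenarios, completed before and after training.

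**The concern.** Early detection and the contribution of training are two specific claims. The first needs a measure that places detection in time, for example against onset, severity or earlier contacts with services. The second needs a contrast in which training varies and the registry does not. The stated outcomes supply neither for detection in practice.

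Training, and the attention that comes with being monitored, can lower the threshold at which a professional records a suspicion. The reporting rate would then rise even if no additional true case were found. The article presents the pilot as groundwork for regional and national expansion, so a rise in reports described as earlier detection due to training could be carried forward as a finding that the data do not contain.

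**Working it through.** **Step 1. Does any stated outcome measure earliness?**

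- *Number and rate of reports:* a volume, with no timing relative to the course of the case.
- *Reporting timeliness:* listed without a definition. The only latency the article describes (System-Level Impact and Future Perspectives; Principal Findings) runs from suspicion to formal report. On that reading the clock starts once the case has already been detected.
- *Pathway activation, follow-up documentation, duplicates:* process measures of what happens after a report.
- *Report-quality indicators in Registry Phase Results:* completeness, traceability, documented actions, follow-up fields and pathway activation. All are process measures.
- *Scenario tests:* recognition on paper cases, not detection in practice.

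None dates detection.

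**Step 2. Can the rate separate better recognition from a lower threshold?**

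The plan states no expected rate, IRR or share of suspicions upheld, so there is no figure of its own to reproduce. The inputs below are assumptions, and equal professional-time is assumed in the count example.

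Let *p* be the share of reports upheld before implementation, *R* the IRR for all reports, and *q* the share upheld among the extra reports. Suppose the reports that would have been made anyway are upheld as before. Then:

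- ratio of upheld-report rates = (*p* + (*R* − 1)*q*) / *p*
- share upheld afterwards = (*p* + (*R* − 1)*q*) / *R*

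With *p* = 0.50 and *R* = 1.5:

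| Extra reports | Upheld-rate ratio | Share upheld after |
|---|---|---|
| none upheld (*q* = 0) | 0.50/0.50 = 1.0 | 0.50/1.5 = 33% |
| upheld as before (*q* = 0.50) | 0.75/0.50 = 1.5 | 0.75/1.5 = 50% |
| all upheld (*q* = 1) | 1.00/0.50 = 2.0 | 1.00/1.5 = 67% |

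The planned IRR is 1.5 in every row.

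Over *p* from 0.30 to 0.70 and *R* from 1.25 to 2.0:

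- With *q* = 0, the upheld-rate ratio is always 1.0. The share upheld afterwards lies between 0.30/2.0 = 15% and 0.70/1.25 = 56%.
- With *q* = 1, the upheld-rate ratio lies between (0.70 + 0.25)/0.70 = 1.36 and (0.30 + 1.0)/0.30 = 4.33.

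In counts: 20 reports before with 60% upheld, and 30 after with 40% upheld, give an IRR of 30/20 = 1.50. The ratio for upheld reports is (30 × 0.40)/(20 × 0.60) = 12/12 = 1.00.

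The planned sensitivity analyses remove or collapse duplicates. They do not address suspicions later set aside.

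**Step 3. Can the rate isolate training?**

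Study Design places training before activation of registry data entry, and the post-implementation rate is observed after both. Participants and Recruitment excludes those who do not complete training, so there is no untrained group using the registry. The pre/post rate is the effect of the combined system plus anything else that changed over the period.

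The scenario tests are different. They are taken immediately after training and before live registry use, although training itself includes hands-on registry sessions. They can speak to change in tested recognition after training.

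**The case against.** The strongest defence is that the plan does not rest on report volume alone. The measure is a rate, per contact where possible. Recognition is tested directly with clinical scenarios. Registry Phase Results already says that cases will be described by outcome. The stated target is suspicion, so counting suspicions matches the secondary objective on reporting rates. The rate is a secondary outcome of a pilot, and both Sample Size Calculation and the disputed sentence itself call the evidence preliminary or non-definitive.

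Much of this stands, and it rules out several stronger readings:

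- *A reader might infer that the plan would count over-reporting as success.* The documents do not say so. No direction or threshold of the rate is declared a success, and tests are 2-tailed. The article frames underreporting as the problem and does not mention over-reporting, which invites that reading of a higher IRR but does not prescribe it.
- *A reader might infer that nothing supports any claim about training.* The scenario tests do support one, limited to tested ability.
- *A reader might infer that the share of suspicions upheld can simply be tabulated before and after.* No section says that the case management outcome field records whether a suspicion was supported, or that comparable outcomes exist for the baseline period.
- *A reader might take it as settled that timeliness is measured from suspicion.* That comes from the expected-impact text, not from an outcome definition, which a full protocol may hold.

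The core remains. Calling evidence preliminary qualifies its strength, not what it measures. A test score is not detection in practice, and pathway activation is an action taken, not confirmation of the suspicion.

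**Conclusion.** The claim in Overall Evaluation Outcomes, and the first hypothesis behind it, go beyond what the stated measures can show. Earliness is not measured by any listed outcome. The reporting rate cannot tell better recognition from a lower threshold, and it cannot separate training from the registry. The scenario tests support a statement about tested recognition ability and no more.

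The ambiguity could be large: under the assumed range, the same IRR of 1.25 to 2.0 fits an upheld-rate ratio of 1.0 as well as a real gain. This shows what the rate cannot rule out. It does not show that over-reporting is likely here, because the documents give neither a reporting rate nor a share upheld.

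The primary usability outcome is unaffected. The correction should be made because it changes what the study may conclude, and because the article reports that data analysis has not started.

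**What to change.** 1. In Overall Evaluation Outcomes, replace the reference to training's contribution to early detection with: *change in tested recognition ability after training, and change in the rate of suspected maltreatment reports after the combined registry-training system*.
2. In the Statistical Analysis overview and Registry Phase Results, present the IRR beside the distribution of recorded case management outcome for post-implementation records, with pending records shown as their own category. If the field records whether the suspicion was supported, give that share with a 95% CI.
3. State that a higher IRR alone is not evidence of better or earlier detection.
4. Give an IRR for supported reports only if comparable baseline outcomes exist. This would help with the threshold question but does nothing for earliness, which only the narrower wording resolves.

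The cost is a narrower claim and one small tabulation from a field already planned. How informative the tabulation is depends on how that field is coded and on how many records are still pending at the end of follow-up.
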